## Abstract

**Background:**

Post-stroke cognitive impairment (PSCI) is common. However, the underlying pathophysiology remains largely unknown. Understanding the role of microvascular changes and finding markers that can predict PSCI, could be a first step towards better screening and management of PSCI. Capillary dysfunction is a pathological feature of cerebral small vessel disease and may play a role in the mechanisms underlying PSCI. Extracellular vesicles (EVs) are secreted from cells and may act as disease biomarkers. We aim to investigate the role of capillary dysfunction in PSCI and the associations between EV characteristics and cognitive function one year after acute ischemic stroke (AIS) and transient ischemic attack (TIA).

**Methods:**

The ENIGMA study is a single-centre prospective clinical observational study conducted at Aarhus University Hospital, Denmark. Consecutive patients with AIS and TIA are included and followed for one year with follow-up visits at three and 12 months. An MRI is performed at 24 h and 12 months follow-up. EV characteristics will be characterised from blood samples drawn at 24 h and three months follow-up. Cognitive function is assessed three and 12 months after AIS and TIA using the Repeatable Battery for the Assessment of Neuropsychological Status.

**Discussion:**

Using novel imaging and molecular biological techniques the ENIGMA study will provide new knowledge about the vascular contributions to cognitive decline and dementia.

**Trial registration:**

The study is retrospectively registered as an ongoing observational study at ClinicalTrials.gov with the identifier NCT06257823.

## Introduction and rationale

We continue to live longer, and the impact of age-related diseases such as stroke and dementia is growing [1]. In addition to the functional disability a stroke may cause, cognitive impairment after stroke is common. Post-stroke cognitive impairment (PSCI) is observed in up to 50% of stroke survivors, and a stroke doubles the risk of dementia [2–4]. Persistent cognitive impairment has also been found in patients with transient ischemic attack (TIA) [5], a disorder that is considered reversible by definition.

PSCI and dementia are associated with increased morbidity and mortality [6–8], however no specific disease modifying management exist. This has urged stakeholders to call for more research into the epidemiology, risk-factors, biomarkers, and mechanisms underlying PSCI [9, 10].

Many risk factors for PSCI have been identified including stroke severity, lesion size and location and common vascular risk factors such as age, hypertension, diabetes, atrial fibrillation, and smoking [5, 11–13]. Further, some magnetic resonance imaging (MRI) markers have been associated with PSCI including brain atrophy and markers of cerebral small vessel disease (cSVD) such as white matter hyperintensities and cerebral microbleeds [14, 15]. In addition, several blood-derived biomarkers have also shown promise as predictors of PSCI [16–18]. Despite these advances in the field, the exact underlying pathophysiology behind PSCI is not well understood. Identification of early pathologic changes associated with PSCI could be a first step in the development of a prognostic aid and in identifying future therapeutic targets.

Cerebral capillary dysfunction is characterized by limited oxygen extraction from the brain capillaries due to age- and risk factor-related capillary flow heterogeneity [19]. Capillary dysfunction is a pathophysiological feature of cSVD and may play an important role in the vascular mechanisms underlying PSCI [20, 21]. Advanced perfusion magnetic resonance imaging (MRI) techniques can detect and quantify capillary dysfunction and may help identify markers of PSCI [22–24].

Extracellular vesicles (EVs) are cell-derived membrane-enclosed vesicles (40-1000 nm diameter) secreted by most cell types including neurons and endothelial cells. They are involved in cell-to-cell communication and can cross the blood brain barrier [25]. The content, surface markers and release of EVs (hereafter called EV characteristics) are altered during disease processes. Because of their potential as diagnostic and prognostic biomarkers, EVs have recently become a field of interest [26]. Studies suggest that EV characteristics may change during acute stroke, in the chronic stroke phase and according to the level of cSVD [27–29]. However, associations between EV characteristics and post-stroke cognition are largely unstudied.

With this prospective clinical observational study, we aim to investigate the role of capillary dysfunction in PSCI and to examine the associations between EV characteristics and cognitive function after acute ischemic stroke (AIS) and TIA.

## Methods

### Design

The ENIGMA study is a single-centre prospective clinical observational study.

### Patient population

Patients aged ≥ 60 years admitted with AIS or TIA within 24 h of symptom onset and with a clinically relevant diffusion restriction identified on MRI diffusion weighted-imaging (DWI) are eligible for inclusion. Patients are enrolled from the comprehensive stroke center at Aarhus University Hospital in Denmark from April 2021 to June 2024, with last follow-up expected in June 2025. Detailed inclusion and exclusion criteria are summarized in Table 1.

A subset of patients participated in the clinical randomized controlled trial, Remote Ischemic Conditioning for Acute Stroke (RESIST) [30].

**Table 1 Tab1:** Eligibility criteria

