**Inclusion criteria**
• AIS or TIA with a clinically relevant diffusion restriction identified on MRI DWI-sequence on admission
• Admittance within 24 h from symptom onset
• Age ≥ 60

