### Study procedures and follow-up

Eligible patients are included within the first 24 h of admission. Baseline measurements are carried out within 48 h from admission. In-person follow-up visits are conducted three months (+/- 1 week) and 12 months (+/- 2 weeks) after inclusion. An MRI is performed in extension to the 12-month follow-up visit. If patients decline to participate in the MRI or if they have incurred contraindications to undergo MRI, they are still eligible for the 12-month follow-up visit. In addition, long-term register-based follow-up is planned. It will include follow-up for recurrent stroke, other vascular events, vascular death, and dementia. Study procedures and their timings are listed in Table 2. Figure 1 illustrates anticipated patient inclusion and follow-up.

**Table 2 Tab2:** Study assessments and registrations

Assessment/registration	Baseline	3-month follow-up	12-month follow-up	Long-term follow-up
Demographics	x			
Medical history	x			
Medication use	x			
Admission NIHSS score	x			
Symptom onset and admission time	x			
Acute treatment	x			
Standard blood chemistry at admission	x			
Pre-stroke mRS	x			
IQCODE	x			
Height, weight and BP	x	x	x	
Smoking and alcohol use	x			
MoCA	x	x	x	
PASE	x	x	x	
WHO-5	x	x	x	
MDI	x	x	x	
Educational level	x			
New vascular events		x	x	x
Functional outcome: mRS		x	x	
Stroke classification: TOAST and OSCP		x		
RBANS		x	x	
Blood sample for EVs*	x	x		
Blood sample for APOE genotyping		x		
MRI**	x		x	
Dementia				x

**Blood sample for EVs is drawn 24 h (+/- 8 h) after admission*

***Baseline MRI is performed 24 h (+/- 6 h) after acute MRI on admission*

*NIHSS: National Institutes of Health Stroke Scale, mRS: modified Rankin scale, IQCODE: Informant Questionnaire on Cognitive Decline in the Elderly, BP: blood pressure, MoCA: Montreal Cognitive Assessment, PASE: Physical Activity Scale for the Elderly, WHO-5: World Health Organisation Five Well-Being Index, MDI: Major Depression Inventory, TOAST: trial of Org 10,172 in Acute Stroke Treatment, OSCP: Oxfordshire Community Stroke Project Classification, RBANS: Repeatable Battery for the Assessment of Neuropsychological Status, EVs: extracellular vesicles, APOE: apolipoprotein E, MRI: magnetic resonance imaging*

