### Statistical analysis

The role of capillary dysfunction on PSCI will be assessed by the association between CTH at baseline and PSCI. The primary outcome will be the difference in total RBANS score from three to 12 months follow-up. Secondary outcomes include total RBANS score at 12 months follow-up, difference in MoCA score from three to 12 months follow-up, and MoCA score at 12 months follow-up. All associations will be assessed using linear mixed effects models adjusting for age, sex, educational level, baseline NIHSS, smoking, and diabetes. Analyses will be stratified by APOE genotype (ε4 carriers vs. non-carriers) and pre-stroke cognitive decline (IQCODE > 3.48 vs. IQCODE ≤ 3.48) to assess for effect modification by these factors. Level of cSVD will be assessed as a mediator.

Associations between EV characteristics and cognitive function after stroke will be assessed primarily by exploring differences in EV characteristics at baseline between patients with normal cognition, impaired cognitive function (total RBANS index score 70–85) and reduced cognitive function (total RBANS index score < 70) at 12-month follow-up using analysis of differential expression. Secondary analyses include exploring differences in EV characteristics at baseline among patients with a decline (≥ 6 points) versus patients with no decline in total RBANS score from three to 12 months, between patients with decline (≥ 2 points) versus no decline in MoCA score from three to 12 months follow-up, and between patients above and below MoCA score of 22 and 26 at 12-months follow-up. Analyses will be adjusted for age, sex, educational level, baseline NIHSS, diabetes, and hypertension. In addition, analyses stratified by APOE genotype, pre-stroke cognitive decline, and level of cSVD will be performed.

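### The covariate lists omit time from onset to the EV sample, which can run from 16 to 56 h, and RESIST status; both are cheap to add, and the size of any bias is unknown

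*Protocol article*

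**What the plan says.** All references are to the protocol article.

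- **Entry (Table 1, Inclusion criteria):** "Admittance within 24 h from symptom onset".
- **EV sample (Table 2 footnote, repeated in the blood sample section):** "Blood sample for EVs is drawn 24 h (+/- 8 h) after admission".
- **Baseline scan (Table 2 footnote, repeated under Magnetic resonance imaging):** "Baseline MRI is performed 24 h (+/- 6 h) after acute MRI on admission".
- **General limit (Study procedures and follow-up):** "Baseline measurements are carried out within 48 h from admission".
- **Time dependence (Introduction and rationale):** "Studies suggest that EV characteristics may change during acute stroke". The sentence goes on to the chronic phase and to the level of small vessel disease. Nothing comparable is said about CTH.
- **Co-enrolment (Patient population):** "A subset of patients participated in the clinical randomized controlled trial, Remote Ischemic Conditioning for Acute Stroke (RESIST"). RESIST is not mentioned again.
- **CTH analysis (Statistical analysis):** "The role of capillary dysfunction on PSCI will be assessed by the association between CTH at baseline and PSCI". The covariates are age, sex, education, NIHSS, smoking and diabetes.
- **EV analysis (Statistical analysis):** "Analyses will be adjusted for age, sex, educational level, baseline NIHSS, diabetes, and hypertension".
- **Strata:** APOE genotype and pre-stroke cognitive decline for both analyses, and small vessel disease level for EVs.

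Table 2 shows that onset and admission times are recorded. Neither time since onset nor RESIST status appears as a covariate, a stratum or a sensitivity analysis.

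**The concern.** Both baseline markers are anchored to hospital events, the EV sample to admission and the scan to the admission MRI. Two patients whose samples are both labelled 24 h can therefore be at quite different points after the stroke.

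In the EV analysis the marker is compared across cognitive groups defined at 12 months. Variation due to sampling time goes into the residual if it is balanced across those groups, and into the group difference if it is not. In the second case a marker of sampling phase could be reported as a marker of post-stroke cognitive impairment.

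RESIST raises a related question. Some patients were randomised to an intervention for acute stroke. If that intervention shifted a baseline marker and also later cognition, it would be a common cause of exposure and outcome. Patients who joined RESIST may also differ from those who did not, and that contrast is not randomised.

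Because the article writes out its covariate lists, this is a matter of how a stated model is specified, not only of detail left for later.

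**Working it through.** **1. Onset-to-measurement windows**

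Inputs: onset to admission 0 to 24 h; admission to EV sample 24 − 8 = 16 h to 24 + 8 = 32 h; admission MRI to baseline MRI 24 − 6 = 18 h to 24 + 6 = 30 h.

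| Measure | Earliest after onset | Latest after onset |
|---|---|---|
| EV sample | 0 + 16 = 16 h | 24 + 32 = 56 h |
| CTH scan | 0 + 18 = 18 h, plus delay to first MRI | 24 + 30 = 54 h, plus delay to first MRI |

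The ratio of the EV extremes is 56/16 = 3.5. The delay from admission to the first MRI is not stated. The general limit of 48 h from admission caps any baseline measure at 24 + 48 = 72 h after onset. These are outer limits; the document gives no distribution within them.

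**2. The plan's own sample size**

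The plan states 71 patients for 10 predictors, 90% power and significance level 0.05, with no numerical effect size. It can therefore only be solved backwards. In the pwr form, lambda = f² × (u + v + 1). With u = 10 and v = 60, N = 71 corresponds to f² = 0.335, R² = 0.335/1.335 = 0.251 and r of about 0.50. If CTH is instead tested on 1 df among 10 predictors, N = 71 corresponds to f² = 0.175, a partial r of about 0.39. Which test was meant is not stated.

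**3. Cost in degrees of freedom**

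Assume that each listed covariate takes 1 df. CTH plus six covariates makes 7 predictors. RESIST status in three levels (not enrolled, control, conditioning) adds 2, giving 9. A linear time term adds 1, giving 10, the number budgeted.

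For a 1-df test at N = 100 and 90% power, with v = 100 − k − 1 and lambda = f² × (v + 2), partial r = √(f²/(1 + f²)):

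| Predictors k | v | f² | Detectable partial r |
|---|---|---|---|
| 7 | 92 | 0.1142 | 0.320 |
| 9 | 90 | 0.1167 | 0.323 |
| 10 | 89 | 0.1180 | 0.325 |

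With lambda = f² × N instead, the value is 0.311 for both 7 and 10 predictors. Even if the 10 budgeted predictors were already used and two more were added, the back-solved omnibus effect would need 77 patients, against 100 planned.

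The budget of 10 was set for the CTH model. The main EV comparison has three cognitive groups (2 df) and six covariates, so it goes from 8 to 11 df. Residual df at N = 100 go from 91 to 88.

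**4. Possible gain in precision (assumption only)**

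The document does not say how much marker variance these factors explain. If it were 10%, the residual SD would be multiplied by √0.90 = 0.949, a fall of about 5%. If it were 20%, the factor is √0.80 = 0.894, a fall of about 11%.

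**The case against.** Several points on the other side carry weight.

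- **The statement about EVs is general.** It speaks of change during acute stroke and in the chronic phase. It does not say that EVs drift hour by hour between 16 and 56 h. This stands: the statement makes time dependence plausible but does not show it.
- **Confounding by time is conditional.** Onset-to-sample time would have to relate to cognition after adjustment for NIHSS and the other covariates, and NIHSS already takes up part of any difference in severity between early and late presenters. Without such a link, time only adds noise, which costs precision or attenuates an association and does not create one. This stands.
- **Little is known about RESIST from this document.** The size of the subset, the allocation split, and the timing of conditioning relative to the sample and scan are not given. Allocation is randomised, so it confounds only if conditioning affects both marker and cognition. This stands.
- **The article is condensed.** Co-enrolment and sampling-time analyses are often set in an analysis plan, and the predictor budget leaves room for further terms. This stands only in part, because the article commits to two explicit lists and named strata that leave both factors out.

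A reader might infer that the EV and CTH results will be biased, or that RESIST has contaminated the cohort. The documents support neither reading. Nor does the 16 to 56 h window apply to CTH, which has its own window and no statement of time dependence behind it.

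**Conclusion.** The point holds as a cheap improvement to a stated model. Onset-to-sample time can differ by up to 40 h (56 − 16) between patients, the article itself gives a reason why the acute phase may matter for EVs, and the EV covariate list omits it. Both lists also omit participation in a randomised acute-stroke trial that the article discloses.

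The conclusion goes no further than this. For EVs, time since onset is at least avoidable noise if the markers vary over that window. It is a confounder only if it relates to cognition given the other covariates. RESIST allocation is a confounder only if conditioning acts on both marker and cognition. Neither bias can be computed from the document, and the 5% to 11% fall in residual SD rests on an assumed 10% to 20% of explained variance. Adjusting CTH for time to scan also rests on an assumption, so it belongs in a sensitivity analysis.

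**What to change.** Before the analysis, amend the covariate specification as follows.

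1. **EV models:** add hours from symptom onset to blood sample as a covariate.
2. **EV and CTH models:** add RESIST status in three levels (not enrolled, control, conditioning). Alternatively, run a sensitivity analysis that excludes patients allocated to conditioning.
3. **CTH model:** add hours from onset to baseline MRI in a sensitivity analysis, labelled as resting on the assumption that CTH varies over the window.
4. **Reporting:** give the number of patients in each RESIST category and the distribution of onset-to-sample and onset-to-MRI times by outcome group.

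The cost is 1 df for time and 2 df for RESIST status, which moves the detectable partial r at 100 patients from about 0.320 to at most about 0.325 in the CTH model. Onset and admission times are already collected. The actual sampling and scan times and the allocation codes from RESIST are also needed. No change to recruitment or procedures follows. Setting this in advance also avoids the appearance of a data-driven adjustment later.

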**Inclusion criteria**
• AIS or TIA with a clinically relevant diffusion restriction identified on MRI DWI-sequence on admission
• Admittance within 24 h from symptom onset
• Age ≥ 60
**Exclusion criteria**
• Dependency in activities of daily living (mRS score > 2)
• Known dementia, neurodegenerative disease, or other significant brain disease
• Concomitant life-threatening disease
• Contraindications to undergo MRI
• Allergy or intolerance to MRI contrast agents
• eGFR < 30
• Unable to give written informed consent
• Deemed unfit for follow-up

*AIS: acute ischemic stroke, TIA: transient ischemic attack, MRI: magnetic resonance imaging, DWI: diffusion-weighted imaging, mRS: modified Rankin scale, eGFR: estimated glomerular filtration rate*

### Protocol approvals and patient consent

The study is approved by the Danish regional research ethics committee (ID: VEK 1-10-72-253-20). The study is conducted according to the declaration of Helsinki. All patients provide written informed consent before enrollment.

### Study objectives

Primary objectives.

To investigate associations between capillary dysfunction and PSCI.To investigate the associations between EV characteristics and PSCI.

Secondary objectives.

To investigate associations between capillary dysfunction and functional outcome, well-being, and depression after stroke.To investigate the associations between EV characteristics and functional outcome, well-being, and depression after stroke.

### Study procedures and follow-up

Eligible patients are included within the first 24 h of admission. Baseline measurements are carried out within 48 h from admission. In-person follow-up visits are conducted three months (+/- 1 week) and 12 months (+/- 2 weeks) after inclusion. An MRI is performed in extension to the 12-month follow-up visit. If patients decline to participate in the MRI or if they have incurred contraindications to undergo MRI, they are still eligible for the 12-month follow-up visit. In addition, long-term register-based follow-up is planned. It will include follow-up for recurrent stroke, other vascular events, vascular death, and dementia. Study procedures and their timings are listed in Table 2. Figure 1 illustrates anticipated patient inclusion and follow-up.

**Table 2 Tab2:** Study assessments and registrations

Assessment/registration	Baseline	3-month follow-up	12-month follow-up	Long-term follow-up
Demographics	x			
Medical history	x			
Medication use	x			
Admission NIHSS score	x			
Symptom onset and admission time	x			
Acute treatment	x			
Standard blood chemistry at admission	x			
Pre-stroke mRS	x			
IQCODE	x			
Height, weight and BP	x	x	x	
Smoking and alcohol use	x			
MoCA	x	x	x	
PASE	x	x	x	
WHO-5	x	x	x	
MDI	x	x	x	
Educational level	x			
New vascular events		x	x	x
Functional outcome: mRS		x	x	
Stroke classification: TOAST and OSCP		x		
RBANS		x	x	
Blood sample for EVs*	x	x		
Blood sample for APOE genotyping		x		
MRI**	x		x	
Dementia				x

**Blood sample for EVs is drawn 24 h (+/- 8 h) after admission*

***Baseline MRI is performed 24 h (+/- 6 h) after acute MRI on admission*

*NIHSS: National Institutes of Health Stroke Scale, mRS: modified Rankin scale, IQCODE: Informant Questionnaire on Cognitive Decline in the Elderly, BP: blood pressure, MoCA: Montreal Cognitive Assessment, PASE: Physical Activity Scale for the Elderly, WHO-5: World Health Organisation Five Well-Being Index, MDI: Major Depression Inventory, TOAST: trial of Org 10,172 in Acute Stroke Treatment, OSCP: Oxfordshire Community Stroke Project Classification, RBANS: Repeatable Battery for the Assessment of Neuropsychological Status, EVs: extracellular vesicles, APOE: apolipoprotein E, MRI: magnetic resonance imaging*

**Fig. 1 Fig1:**
[figure not shown]
Anticipated inclusion and patient flow in the ENIGMA study

### Magnetic resonance imaging

An MRI is performed at 24 h (+/- 6 h) after the acute MRI on admission and again at the 12-month follow-up visit. MRI sequences include T1-weighted 3D images for co-registration, DWI, kurtosis diffusion imaging, 3D fluid-attenuated inversion recovery (FLAIR), susceptibility weighted imaging (SWI), and gradient echo (GRE) and spin echo (SE) perfusion imaging.

White matter hyperintensities, visible on FLAIR images, are semi-automatically outlined [31]. Capillary function is characterized by capillary transit time heterogeneity (CTH), parameterized as the standard deviation of blood transit times within each image voxel using SE perfusion imaging [19, 22, 23]. Finally, grey and white matter microstructural integrity, including dendrite density, axonal density and dispersion, and intra- and extra-axonal water diffusivity are characterized based on DWI and kurtosis diffusion imagning [32–35]. All MRI scans are performed on site with a 3T Siemens Magnetom Vida scanner (Siemens Healthcare, Erlangen, Germany).

The burden of cSVD is assessed on the 24-hour and the 12-month MRI scans. A total cSVD score is calculated based on the STRIVE-1 criteria with local specifications [36]. The cSVD score includes number and location of microbleeds, superficial siderosis, number of lacunes, grade of white matter hyperintensities, grade of global cortical atrophy, and enlarged perivascular spaces. Scoring is independently performed by a trained neurologist and a neuroradiologist. At scoring disagreement, consensus is achieved. Table 3 presents an overview of the used MRI sequences.

**Table 3 Tab3:** MRI sequences and characteristics at 24 h and 12 months

Sequence	Description	Purpose
DWI + ADC	Diffusion Weighted Imaging (DWI) and calculated Apparent Diffusion Coefficient (ADC)	Grey and white matter microstructural integrity, including dendrite density, axonal density and dispersion, and intra- and extra-axonal water diffusivity
Kurtosis	Kurtosis diffusion Imaging	
3D FLAIR	3-Dimensional Fluid-Attenuated Inversion Recovery	White matter hyperintensities, perivascular spaces, and lacunes
3D T1 (MP2RAGE)	3-Dimentional T1- magnetization Prepared Rapid Gradient Echo	Atrophy/cortical thickness
SWI	Susceptibility Weighted Imaging	Microbleeds and superficial siderosis
PWI GRE	Gradient Echo Perfusion Imaging	Capillary transit time heterogeneity
PWI SE	Spin Echo Perfusion Imaging	

